#### Sample Size, Power Calculations, and Interim Analyses

The power analysis for our trial was run with G^*^Power 3.1.9.4. In a previous trial, a physiotherapy for functional motor symptoms reached a moderate effect (*f* = 0.33) at 6-month follow-up on the SF-36 Physical Functioning subscale, our primary outcome (23). For this trial we conservatively assume a small group^*^time interaction effect (*f* = 0.10) under consideration of our three measurements and a test-retest reliability of *r* = 0.5. A power analysis for a mixed-effect ANOVA with an alpha error probability of 0.05 and a power of 0.80 results in an optimal total sample size of 164. A dropout rate of 5% is estimated based on our clinical experience and a recently completed trial that evaluated physiotherapy for individuals with FNSD (23). Accordingly a sample size of 172 participants is planned to be recruited.

We will, however, allow eight interim analyses every 22nd patient, conducted by a person who is independent of the day-to-day activities of the trial. Using the Lan-DeMets alpha spending function (55) we have gained appropriate boundaries or *p*-values for each interim analysis that would indicate a necessary stop and would allow an early conclusion of the trial (see Table 3). We used R 4.0.2 (56) and the ldbounds package (57) to gain Lan-DeMets boundaries. This approach helps to control for alpha-error accumulation with repeated interim analyses.

**Table 3 T3:** *P*-values (based on Lan-DeMets alpha spending function) indicating a necessary stop of the trial and needed sample size at each interim analysis.

**Interim analysis**	**Sample size**	***P*-value**
1	22	0.00000003
2	44	0.00009
3	66	0.001
4	88	0.005
5	110	0.013
6	133	0.024
7	155	0.036
8	172	0.050

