#### Statistical Analysis

Analyses will be based on intention-to-treat principles and will be carried out at the end of the last follow-up assessment. We will apply a linear mixed-effect model with baseline adjustment with main effects (fixed effect) for time (level 1, contrasts to baseline at 8- and 16-week follow-up) and group (level 2), group-by-time cross-level interaction term (8- and 16-week follow-up), and a generalized covariance matrix to account for dependency among observations. In order to deal with missing values, maximum likelihood estimation will be applied. Patterns of missing values will be assumed to be random. The outcomes of interest will be the group-by-time interaction at week 8 (hypothesis 1 and 2), and at week 16 (hypothesis 3). Effect sizes (Cohen's d) with 95% CI of changes between baseline and 8- and 16-week follow-up, as well as of between-group differences at 8- and 16-week follow-up will be investigated. Further sensitivity analyses will be conducted depending on the dropout rates and pattern of dropout reasons. For this purpose the linear mixed-effect models described above will be rerun for defined subgroups of the total sample (e.g., for participants with complete datasets only). To test for moderation (exploratory research question) we will add the moderator variable to the linear mixed-effect model described above (level 1: time; level 2: group) and will analyze a 3-level interaction. A significance level of 5% will apply to all analyses. Statistical analyses will be conducted with SPSS.

A limitation of group analyses is that it provides no information about the relative proportions of participants who did or did not respond to a treatment, which is based on a set standard. In accordance with recommendations by the Initiative on Methods, Measurement, and Pain Assessment in Clinical Trials (58), we will compare the distribution of participants with an improvement of at least 30 or 50%, no change, or deterioration on the primary outcome between the study groups with χ^2^-tests. Groups will be compared regarding adverse therapy effects, measured with the Inventory for the Assessment of Negative Effects of Psychotherapy, with independent sample *t*-tests and χ^2^-tests. To assess interrater reliability of the treatment fidelity ratings, intraclass coefficients (two-way random model with measure of agreement) for each item will be computed.

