Besides the strengths, we anticipate several limitations. We have already discussed risks of bias and have implemented tools to reduce these risks. There are additional challenges that we anticipate with implementing the study procedure. First, recruiting from one hospital can limit the representativeness of our sample and can hamper the potential to gain the optimal sample size. The institution where we will conduct our trial covers the neurological rehabilitation of a substantial part of the NZ population, which will ensure our sample is largely representative for the region. We first want to ensure the feasibility of our trial at this site before considering the potential to extend the trial to at least one other site. With a priori planned interim analyses, we will regularly check if the conservative estimation of our optimal sample size will need correction. Second, the design of our active control intervention has several advantages mentioned above. Nonetheless, we have to expect indirect therapeutic effects of our active control treatment (e.g., incidental change in beliefs after re-establishing a normal movement). Even accounting for the active control treatment being potentially less effective than NH-CBT, it seems likely that the mean difference between groups will be small. Our power analysis therefore builds on a conservatively estimated small between-group effect. When designing the control intervention, we also had to consider the pragmatic fact that a treatment-as-usual or a waitlist control group would not have been feasible, because our institution is the only one covering neurorehabilitation for patients from a bigger district in New Zealand, implying limited resources and long waitlists for receiving treatment. Third, another pragmatic limitation is that we have to accept participants in the inpatient and outpatient settings as well as participants of older ages. We will apply statistical strategies to control for the type of treatment setting in our data analysis. We will include older participants only if motor symptoms are considered highly likely to be functional and not related to age-related degenerative processes. Fourth, our 8-week follow-up window after the end of treatment is very short. Again, due to pragmatic reasons associated with delivering both treatments in the context of a clinical service, we would not be able to let our control participants wait for a longer period than this before they receive NH-CBT. At the same time, we consider the *controlled* follow-up assessment as an important strength of our study design. Finally, we will implement several methods to ensure treatment fidelity (e.g., frequent supervision, audio-recording the initial therapy session, and feedback to therapists). However, we will not be able to completely exclude the risk of therapists deviating from our rules of treatment fidelity and exposing participants to distraction techniques or interventions that address illness beliefs.

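### Table 3 gives the cumulative alpha spent at each look as if it were the stopping p-value, so the overall type I error is about 6.5%, not 5%

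*Protocol article*

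**What the plan says.** Under Sample Size, Power Calculations, and Interim Analyses, the article sets the overall error and the fixed-design sample size: "with an alpha error probability of 0.05 and a power of 0.80 results in an optimal total sample size of 164". Allowing for dropout, it plans to recruit 172. It then adds the monitoring plan: "We will, however, allow eight interim analyses every 22nd patient". The boundaries come from the Lan-DeMets approach through the R package ldbounds, and the article concludes: "This approach helps to control for alpha-error accumulation with repeated interim analyses".

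The caption of Table 3 presents its column as p-values at which the trial must stop. The rows are 0.00000003, 0.00009, 0.001, 0.005, 0.013, 0.024, 0.036 and 0.050, at 22, 44, 66, 88, 110, 133, 155 and 172 participants. The section Data and Patients' Safety Monitoring has the monitoring board decide on early termination for benefit from these rules. Neither the spending function nor the sidedness is named.

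Two other places bear on this. Statistical Analysis says: "A significance level of 5% will apply to all analyses". The Discussion says: "With a priori planned interim analyses, we will regularly check if the conservative estimation of our optimal sample size will need correction".

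**The concern.** A spending function gives the total type I error allowed up to a given information fraction. The p-value to compare with at a look is a different quantity, solved from that total and from the correlation between the looks. The two agree at the first look. After that the nominal p-value lies below the cumulative alpha, and the gap widens to the end.

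Table 3 ends at exactly 0.050. The final test at 0.050 has a 5% false-positive probability by itself, and any earlier look that can end the trial for benefit adds to it. The column therefore cannot be a set of 5% boundaries.

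The primary decision rule is at stake. The Discussion expects a small difference between the groups, so a final p-value between the valid boundary and 0.050 is a realistic result. The plan would report it as a positive trial.

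**Working it through.** **Inputs.** Overall alpha 0.05, the eight looks with their sample sizes, and the eight p-values, all from Sample Size, Power Calculations, and Interim Analyses and Table 3. Two assumptions are added: information is proportional to the number of participants analysed, and the test statistics behave as a standard group-sequential normal process with no true effect.

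**Step 1: reproduce Table 3.** The O'Brien-Fleming-type Lan-DeMets function for a total of 0.05 is

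alpha(t) = 2 × [1 − Φ(1.96/√t)].

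At t = 5/8: 1.96/√0.625 = 2.479, giving 0.0132. At t = 7/8: 1.96/√0.875 = 2.095, giving 0.0361. At t = 1: 0.0500. The fourth column below gives all eight. Seven rows agree with Table 3 after rounding. Row 4 agrees by truncation (0.00557 printed as 0.005). The column is cumulative alpha at equal eighths.

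**Step 2: find the valid nominal p-values.** The boundaries z1 to z8 are solved in turn, by recursive numerical integration, so that the probability of crossing by look k equals alpha(t_k). The nominal two-sided p-value is 2 × [1 − Φ(z_k)]. At t = k/8 the z-boundaries are 5.54, 3.92, 3.21, 2.80, 2.54, 2.35, 2.21 and 2.10.

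| Look | n | Table 3 | Cumulative alpha, t = k/8 | Valid nominal p, t = k/8 | Valid nominal p, t = n/172 | Cumulative type I error with Table 3, t = n/172 |
|---|---|---|---|---|---|---|
| 1 | 22 | 0.00000003 | 0.00000003 | 0.00000003 | 0.00000004 | 0.00000003 |
| 2 | 44 | 0.00009 | 0.00009 | 0.00009 | 0.00011 | 0.00009 |
| 3 | 66 | 0.001 | 0.00137 | 0.0013 | 0.0015 | 0.0010 |
| 4 | 88 | 0.005 | 0.00557 | 0.0051 | 0.0056 | 0.0053 |
| 5 | 110 | 0.013 | 0.0132 | 0.0111 | 0.0120 | 0.0147 |
| 6 | 133 | 0.024 | 0.0236 | 0.0186 | 0.0204 | 0.0289 |
| 7 | 155 | 0.036 | 0.0361 | 0.0269 | 0.0288 | 0.0459 |
| 8 | 172 | 0.050 | 0.0500 | 0.0354 | 0.0342 | 0.0645 |

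**Step 3: overall error if Table 3 is used as printed.** Two-sided, it is 0.0660 at t = k/8 and 0.0645 at t = n/172. A simulation of 2 million trials at t = n/172 gave 0.0642. Read as one-sided thresholds, the results are 0.0629 and 0.0616. With unrounded spending values in place of the printed ones, the two-sided error is 0.066 to 0.067.

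**Step 4: other spending choices.** A symmetric design that spends 0.025 on each side has a final nominal p of 0.0388 at t = k/8 and 0.0377 at t = n/172. A one-sided 0.05 design has a final one-sided p of 0.0377 and 0.0366. No variant gives 0.050.

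**Step 5: timing.** The listed sizes correspond to fractions from 22/172 = 0.128 to 155/172 = 0.901, not 0.125 to 0.875. At the seventh look the spending curve at the real fraction gives 0.039, against 0.036 printed. The eighth look, at 172, is the full planned sample and therefore the final analysis.

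**Step 6: power.** For a single-contrast z-test with 80% power in a fixed design, the valid boundaries of Step 2 give about 78%. The symmetric version gives about 79%.

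**The case against.** The article says only that the approach helps to control error accumulation, and it does help. Eight unadjusted looks at 0.05 would give about 17.6% at equal spacing, so Table 3 removes most of the inflation. Up to look 7 the cumulative error is about 4.6%, so stopping at the interim looks alone stays under 5%. The breach arises at the last row. This is a fair account of the size, but the printed rule still does not hold the 5% it was built to hold.

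Sidedness is not stated, so one figure claims too much. That stands: the range is about 6.2% to 6.7%, and the corrected final threshold depends on choices the sponsor must declare. The conclusion is the same under each.

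The mismatch in timing hardly matters. That also stands: using the real fractions moves the error from 6.6% to 6.45%, slightly downward.

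The Discussion sentence on correcting the sample size may only describe early stopping when the effect is larger than assumed, and no rule for increasing the sample is given. It is ambiguous and separate from the error in Table 3.

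The monitoring board has the final say, so stopping may not be automatic. However, the caption calls each value a necessary stop. The final analysis at 0.050 does not depend on the board in any case.

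An unseen analysis plan could hold other boundaries, but the article prints specific thresholds for a stated use, and those thresholds are wrong.

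**Conclusion.** The concern holds. The p-value column of Table 3 is the cumulative alpha spent, presented as the threshold for stopping. Used as written, the overall two-sided type I error is 6.45% at the stated sample sizes and 6.6% at equal spacing, an excess of about 1.5 percentage points. Looks 1 to 4 are essentially unaffected. Measured against the table's own spending curve, looks 5 to 8 are too lenient, and the last row, together with the 5% level in Statistical Analysis, does the damage. A valid final two-sided threshold lies between 0.034 and 0.039, depending on the spending version and the information fractions. These figures assume information proportional to participants analysed and that every listed look is a binding efficacy test. The power figure is illustrative, because the article's 80% refers to a three-occasion ANOVA interaction.

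**What to change.** 1. Replace the p-value column of Table 3 with nominal p-values computed from the z-boundaries that ldbounds returns, not from its cumulative exit probabilities. If cumulative alpha is also shown, give it a separate, labelled column.
2. Name the spending function and the sidedness. Compute the boundaries at the actual information fractions, preferably counting participants with an evaluable week-8 outcome, and recompute them if the looks fall elsewhere.
3. Describe the plan as seven interim analyses and one final analysis.
4. Amend the 5% statement in Statistical Analysis so that the primary test at the final look uses its own boundary (0.034 to 0.039 two-sided, depending on item 2).
5. As a smaller point, clarify the Discussion sentence: state that the maximum sample size will not be changed on unblinded interim results, or limit the check to blinded variance estimates.

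The cost is a re-run of existing R code, one table column and three or four sentences. The stricter final threshold costs about two points of power at the planned size. No change to recruitment or data collection is needed. The correction should be made before any look at which the printed values would be applied.

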#### Statistical Analysis

Analyses will be based on intention-to-treat principles and will be carried out at the end of the last follow-up assessment. We will apply a linear mixed-effect model with baseline adjustment with main effects (fixed effect) for time (level 1, contrasts to baseline at 8- and 16-week follow-up) and group (level 2), group-by-time cross-level interaction term (8- and 16-week follow-up), and a generalized covariance matrix to account for dependency among observations. In order to deal with missing values, maximum likelihood estimation will be applied. Patterns of missing values will be assumed to be random. The outcomes of interest will be the group-by-time interaction at week 8 (hypothesis 1 and 2), and at week 16 (hypothesis 3). Effect sizes (Cohen's d) with 95% CI of changes between baseline and 8- and 16-week follow-up, as well as of between-group differences at 8- and 16-week follow-up will be investigated. Further sensitivity analyses will be conducted depending on the dropout rates and pattern of dropout reasons. For this purpose the linear mixed-effect models described above will be rerun for defined subgroups of the total sample (e.g., for participants with complete datasets only). To test for moderation (exploratory research question) we will add the moderator variable to the linear mixed-effect model described above (level 1: time; level 2: group) and will analyze a 3-level interaction. A significance level of 5% will apply to all analyses. Statistical analyses will be conducted with SPSS.

A limitation of group analyses is that it provides no information about the relative proportions of participants who did or did not respond to a treatment, which is based on a set standard. In accordance with recommendations by the Initiative on Methods, Measurement, and Pain Assessment in Clinical Trials (58), we will compare the distribution of participants with an improvement of at least 30 or 50%, no change, or deterioration on the primary outcome between the study groups with χ^2^-tests. Groups will be compared regarding adverse therapy effects, measured with the Inventory for the Assessment of Negative Effects of Psychotherapy, with independent sample *t*-tests and χ^2^-tests. To assess interrater reliability of the treatment fidelity ratings, intraclass coefficients (two-way random model with measure of agreement) for each item will be computed.

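### The named week-8 test is an unadjusted change-score comparison, so the promised baseline adjustment adds nothing and available precision is forgone

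*Protocol article*

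**What the plan says.** In the protocol article, the Statistical Analysis section sets one model for the primary outcome: a "linear mixed-effect model with baseline adjustment with main effects (fixed effect) for time (level 1, contrasts to baseline at 8- and 16-week follow-up", followed by "and group (level 2), group-by-time cross-level interaction term (8- and 16-week follow-up), and a generalized covariance matrix to account for dependency among observations". The tests are then named: "The outcomes of interest will be the group-by-time interaction at week 8 (hypothesis 1 and 2), and at week 16 (hypothesis 3". On estimation it says: "In order to deal with missing values, maximum likelihood estimation will be applied".

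It does not say how the baseline adjustment enters the model. It lists no baseline-by-time term and does not constrain the arms to a common baseline mean.

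The section Sample Size, Power Calculations, and Interim Analyses treats baseline in the same way. The trial is sized on an "interaction effect (*f* = 0.10") "under consideration of our three measurements" and a "test-retest reliability of *r* = 0.5". This gives 164 participants, raised to 172 for dropout.

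**The concern.** A contrast against baseline requires baseline to be one of the response rows. Once the group main effect is also in the model, each arm has its own free baseline mean, and the week-8 interaction measures only how much more one arm changed than the other. The sentence promises an adjustment that its own test does not deliver.

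Two things are at stake. The first is precision: the baseline score is collected before randomisation, but the primary contrast subtracts it with a fixed weight of one and does not condition on it. The second is clarity: the primary test should have a single meaning before the first interim look, planned at 22 patients.

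**Working it through.** **1. The plan's own figure.** For the within-between interaction, the noncentrality is f²·N·m/(1−r) = 0.01 × 164 × 3 / 0.5 = 9.84, with 2 and 2(164−2) = 324 degrees of freedom. Power is 80.5% at N = 164 and 79.98% at N = 162, so 164 is reproduced as the smallest even total. Allowance for dropout: 164 × 1.05 = 172.2, in line with 172.

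**2. What the week-8 interaction estimates.** Write the control means as μ0, μ8, μ16 and the NH-CBT means as μ0+γ, μ8+γ+δ8, μ16+γ+δ16. The six means are saturated, so with complete data the estimate of δ8 is (week 8 − baseline in NH-CBT) − (week 8 − baseline in control). If a term β × baseline is added to every row of a participant, the same amount enters the week-8 and the baseline row and cancels from δ8.

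A fit to one simulated complete dataset agrees:
- raw difference in mean change: 0.2564
- interaction without the baseline covariate: 0.2564
- interaction with the baseline covariate: 0.2564
- random-intercept standard error: 0.1387 with and without the covariate
- estimate that does condition on baseline (ANCOVA): 0.2453

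**3. Variance.** With equal variances and correlation r between occasions, the variance per participant, in units of the outcome variance, is:
- change score: 2(1−r) = 1.00 at r = 0.5
- conditioned on baseline: 1−r² = 0.75 at r = 0.5

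The ratio 1.00/0.75 = 1.33 means that the change score needs about one third more participants for the same precision. At r = 0.5 the change score is also no more precise than the week-8 score alone, whose variance is 1.

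**4. From f to a week-8 difference.** The protocol gives no such difference, so a time pattern has to be assumed.
- Full effect at weeks 8 and 16: f² = d²/18, so d = 0.10 × √18 = 0.424.
- Linear build-up to week 16: f² = d16²/24, so d16 = 0.490 and the week-8 difference is 0.245.

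**5. Power at week 8** (82 per arm; two-sided 5% assumed, because sidedness is not stated; interim looks ignored). The standard error is √(2 × 1.00/82) = 0.156 for change and √(2 × 0.75/82) = 0.135 with conditioning.
- Full effect, change: 0.424/0.156 − 1.96 = 0.76, power 77.5%.
- Full effect, conditioned: 0.424/0.135 − 1.96 = 1.18, power 88.0%.
- Linear build-up: 34.8% against 44.1%, a gap of 9.3 points.

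A simulation of 20,000 trials for the full effect gave 77.2% and 87.5%. At N = 172 the full-effect figures are 79.4% and 89.5%.

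**6. Range over r** (full effect at week 8, N = 164):

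| r | 2(1−r) | 1−r² | Power, change | Power, conditioned | Gap (points) |
|---|---|---|---|---|---|
| 0.3 | 1.40 | 0.91 | 63.2% | 81.3% | 18.1 |
| 0.4 | 1.20 | 0.84 | 69.8% | 84.2% | 14.4 |
| 0.5 | 1.00 | 0.75 | 77.5% | 88.0% | 10.5 |
| 0.6 | 0.80 | 0.64 | 85.9% | 92.4% | 6.5 |
| 0.7 | 0.60 | 0.51 | 93.9% | 96.7% | 2.8 |

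**7. One combination to avoid.** Suppose the baseline score is a covariate and also a response row, and the covariance is unstructured. A slope of 1 then makes every baseline residual zero, and the likelihood has no upper bound. In the simulated dataset the slope went to 1, the baseline residual variance fell below 1e-13, and the log-likelihood climbed from −401 to above +1270. Without the covariate the same fit was stable at −586.8.

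**The case against.** The other side has four good arguments.

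- **Estimability.** A reader might infer that the planned model cannot be fitted. The text does not support that. It does not say that the baseline score is a covariate, and it calls the covariance generalized, not unstructured. The baseline adjustment may simply mean the contrasts to baseline, in which case the fit is stable. A random-intercept model with the covariate also runs. An article may leave these details to the full plan.
- **Planned power.** A reader might infer that the trial loses 10 points from its 80%. It does not. The sample size already rests on an interaction with baseline as one of three measurements, so design and analysis agree on this point. The step from 80.5% to 77.5% comes from testing a single week-8 contrast in place of the two-degree-of-freedom interaction. The low figures under linear build-up come from the assumed time pattern. Neither is caused by the handling of baseline.
- **Validity.** A reader might infer bias from chance baseline imbalance. Under randomisation the change-score difference is unbiased on average and the type I error is controlled. What is lost is precision.
- **Size.** The value d = 0.424 is not in the protocol, and 10 points is one scenario.

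All four stand and limit the point. They do not remove it. The article itself names the test, the reference level and the group main effect, and on either reading of the baseline adjustment the week-8 interaction is the change-score contrast. A baseline-by-time term or a common baseline mean would change that. Neither is written, and the listed group main effect conflicts with the second.

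**Conclusion.** The point holds as forgone efficiency and an unclear specification, not as an invalid or underpowered primary test. As written, the week-8 test is the unadjusted difference in change: exactly with complete data, approximately with the expected 5% dropout. At the protocol's r = 0.5, conditioning on baseline would cut the contrast variance by 25%. That is worth about 10 points of power if the full effect is present at week 8, and about 9 if it builds up linearly to week 16. The gain shrinks as r rises. These sizes assume equal variances and correlations across occasions, a two-sided 5% level and one of the two time patterns. The degenerate likelihood is a warning about one possible implementation that the text does not state will be used.

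**What to change.** Rewrite the model sentence in one of two ways.

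1. Take the week-8 and week-16 scores as the responses. Include baseline, baseline-by-time, group, time and group-by-time, with an unstructured covariance. Test the adjusted group difference at week 8 (hypotheses 1 and 2) and at week 16 (hypothesis 3).
2. Keep baseline as a response, constrain the arms to a common baseline mean (no group effect at baseline), and enter no baseline covariate.

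In either case, name the covariance structure and settle the choice before the first interim look. If a full analysis plan already fixes this, align the article's wording with it.

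The cost is a few words and different SPSS syntax, with no new data or patients. The first option drops anyone without a baseline score, which should be rare because baseline assessment precedes randomisation.

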
### Data and Patients' Safety Monitoring

Participants with any type of neurological diagnosis with a range of associated physical disabilities (e.g., weakness, balance difficulties) are at some risk of falling. According to clinical observations, people with FNSD/PMD are at lower risk of injury than people with neurological damage (16). However, there are still some incidents with this group. Treatment necessarily involves taking managed risks whilst ensuring safety, using management strategies and mobility aids. All trial participants will be assessed by a physiotherapist as they start the movement retraining part of the treatment (see *Interventions*) and throughout the treatment if needed, to ensure adequate steps are taken to ensure safety. In the case of serious adverse events (SAE) the Severity Assessment Code (SAC) rating for adverse event reporting (33) will be completed by the therapist. The study therapist has to contact the principal investigator (MR) within 24 h after the event. The PI will not be blinded to the result of the randomization and will therefore be able to decide if the SAE was a serious adverse reaction to the trial treatment.

In order to monitor and supervise the progress of the trial and SAEs associated with the trial treatment, an independent Data Safety and Monitoring Board will be involved, including a psychiatrist, a statistician, a manager of the ISIS Centre and a person who was formerly treated for FNSD at ISIS as a stakeholder of patients' interests. The DSMB will meet on a regular basis and will make final decisions to terminate the trial prematurely for harm, based on their monitoring and evaluation of SAE attributed to our treatment. The SAC rating for adverse event reporting allows for differentiation of four levels of severity of adverse events (34). In the case of severe and major events (SAC 1 and 2), the trial would have to be suspended with immediate effect pending investigation. The DSMB will discuss SAC 3 and 4 events (minor to moderate events), how they relate to our treatment and how they will influence the further course of this trial. The DSMB will also make final decisions to terminate the trial prematurely for benefit, based on stopping rules and interim analyses described below (see *Sample size, power calculations, and interim analyses*).

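### The week-8 effect is to be reported with no stated allowance for the eight-look stopping rule, so the estimate is biased upward, mainly when the trial stops early for benefit

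*Protocol article*

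**What the plan says.** All references are to the protocol article.

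- **Sample Size, Power Calculations, and Interim Analyses, with Table 3.** Analyses are set at 22, 44, 66, 88, 110, 133, 155 and 172 patients. Each has a p-value "that would indicate a necessary stop and would allow an early conclusion of the trial". The last of the eight is the full sample, so seven looks precede it.
- **Data and Patients' Safety Monitoring.** "The DSMB will also make final decisions to terminate the trial prematurely for benefit, based on stopping rules and interim analyses".
- **Sample size.** The planning effect is a group-by-time interaction of f = 0.10, "under consideration of our three measurements and a test-retest reliability of *r* = 0.5". The calculation "with an alpha error probability of 0.05 and a power of 0.80 results in an optimal total sample size of 164", raised to 172 for 5% dropout.
- **Statistical Analysis.** A baseline-adjusted linear mixed model is fitted by maximum likelihood, and hypothesis 1 rests on the interaction at week 8. The reported quantities are "Effect sizes (Cohen's d) with 95% CI of changes between baseline and 8- and 16-week follow-up, as well as of between-group differences", and one 5% level covers every analysis. This section does not refer to the interim looks.

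**The concern.** When a trial stops because its estimate crossed a boundary, that estimate is too large on average. Boundaries on the p-value address type I error; they do not adjust the estimate or its interval. The plan provides for the first and names the second as in a trial with a single analysis.

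The size of the effect matters here. This is a phase II trial, and the Discussion intends a national and international evaluation if efficacy is shown. That next study would probably draw on the d reported here, and an inflated d would make it too small.

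**Working it through.** **1. The plan's own sample size.** For the within-between interaction, λ = f²·N·m/(1−r) = 0.01 × 164 × 3/0.5 = 9.84, with 2 and 2(164−2) = 324 degrees of freedom. Power is 0.805 at N = 164 and 0.7998 at N = 162, so 164 reproduces. Dropout gives 164/0.95 = 172.6, against the 172 stated. This is a rounding matter.

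**2. From f to a week-8 d (assumption).** Let the group differences over the three assessments be (0, d, d). The cell deviations are half of (−2d/3, d/3, d/3), so f² = (1/4)(1/3)(6d²/9) = d²/18. Hence d = 0.10 × √18 = 0.424. The pattern (0, d, 0) gives the same value. A slow build, (0, d/2, d), gives 0.245 at week 8. With r = 0.5 the SD of the change score equals the SD of the outcome, so d is on the same scale for both.

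**3. Smallest d that can stop the trial.** With 1:1 allocation and a normal approximation, d = 2z/√N, where z is the two-sided value for the Table 3 p-value.

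| N | p | z | smallest d |
|---|---|---|---|
| 66 | 0.001 | 3.29 | 0.81 |
| 88 | 0.005 | 2.81 | 0.60 |
| 110 | 0.013 | 2.48 | 0.47 |
| 133 | 0.024 | 2.26 | 0.39 |
| 155 | 0.036 | 2.10 | 0.34 |

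Any stop for benefit at 110 patients or earlier must therefore report more than 0.424. In simulation at d = 0.424, about 41% of all trials stop there.

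**4. Simulation of the rule as printed.** The inputs are independent normal increments, information N/4 and two-sided thresholds from Table 3. At d = 0.424 and N = 172:

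- early stop for benefit: 72.5%;
- mean d in early stops: about 0.556 (0.556/0.424 = 1.31);
- mean d over all trials: about 0.472 (+11%; repeat runs give 11-12%);
- coverage of the ordinary 95% CI: 94.3% overall and about 95.5% in early stops.

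**5. Range over choices the plan leaves open.**

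| Test or pattern | Early stop | Mean overstatement in early stops |
|---|---|---|
| Week-8 change contrast, N 164 to 172 | 70-73% | 31-33% |
| Baseline-adjusted contrast | 81-84% | 21-23% |
| 2-df interaction test | 73-76% | about 25% |
| Slow build (0, d/2, d), week-8 d 0.245 | 30% | 2.05 times the truth |

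If 20 already enrolled patients are added after a stop on the change contrast, the overstatement is about 25-26%. The median overstatement in early stops, for the change contrast at N = 164, is about 23%.

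**6. An effect well below plan.** At an assumed d = 0.20, 22% of trials stop early for benefit. The mean d in those stops is 0.48 (0.48/0.20 = 2.4), and the ordinary CI covers the truth 83% of the time there.

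**7. Table 3 itself.** Cumulative O'Brien-Fleming-type spending is 2(1−Φ(1.96/√t)). At t = k/8 it gives 0.00000003, 0.00009, 0.0014, 0.0056, 0.013, 0.024, 0.036 and 0.050. These match the printed entries, apart from the third and fourth, which are printed as 0.001 and 0.005. Used as nominal p-values, the entries give a two-sided type I error of about 6.4%. Proper boundaries for a 5% design of this kind end near p = 0.037. With such boundaries and a drift set to about 80% power, early stops are 70-72% and the overstatement 30-32%, so the estimation problem does not depend on this error.

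**8. What an adjusted estimator achieves.** These results are for the stage-wise-ordering median-unbiased estimate under the printed boundaries, with d about 0.42.

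| | Unadjusted | Median-unbiased |
|---|---|---|
| Mean bias, all trials | about 12% | about 6% |
| Median bias, all trials | 7% | 0 |
| Root mean squared error | 0.209 | 0.201 |
| 95% CI coverage, all trials | about 94.3% | 95.1% |
| Mean bias in early stops | +31% | about +26% |

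**The case against.** **The article never says the estimate will be unadjusted.** It does not, and estimation after early stopping is often left to an analysis plan or a monitoring charter. This limits the point. It remains that the article itself names the model, the effect measure, the interval and the significance level, and its only stated allowance for repeated looks is on p-values. Followed as written, it gives the biased estimate. The absence of a stated probability of stopping is only missing detail and is not part of this point.

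**A reader might infer that the trial will overstate the effect by a third.** The documents do not support one figure. They give f = 0.10 with no pattern over time, and the baseline adjustment they name lowers the overstatement to 21-23%. It is also a mean over early stops only. Selection on significance inflates any trial: a fixed design of 172 patients at d = 0.42 shows about +13% among its significant results.

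**A reader might infer that the 95% CI is invalid.** At the planned effect it is close to nominal. The 83% figure needs a true d of about 0.20. The Discussion does expect a small between-group difference, but it ties this to the power analysis, that is to f = 0.10. The value 0.20 is therefore an assumption made here, not the plan's expectation.

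**The adjusted estimate does not cure the bias within early stops.** This stands. It corrects the overall distribution and helps only modestly once the trial has stopped.

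**Conclusion.** The point holds as an improvement that should be made. The stated analysis makes no allowance for a stopping rule that, at the planned effect, would end most trials early. On the assumption that f = 0.10 means a week-8 d of about 0.42, 70-84% stop early for benefit, and the unadjusted d is 21-33% too large on average in those stops and 11-12% too large over all trials. If the effect builds slowly, early stops are less frequent (about 30%) and the overstatement in them is about twofold. The bias lies in the point estimate; the interval undercovers after an early stop only if the true effect is well below plan. All figures take the Table 3 entries as two-sided nominal thresholds that are followed whenever crossed.

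**What to change.** 1. Correct Table 3 first, so that it prints nominal stopping p-values and not cumulative alpha spent.
2. In Statistical Analysis, state that the week-8 between-group effect will be given as a stage-wise-ordering median-unbiased estimate with its 95% CI, based on the corrected boundaries. Show the unadjusted d and CI alongside, labelled as unadjusted.
3. State that a result from an early stop will carry a caution that the effect is probably still overstated, and that a later trial should not be sized on it without allowance.

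The cost is a few sentences and a little extra analysis code, with no additional patients. The reported effect will be slightly smaller if the trial stops early.
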